### Setting

RADAR involves collaboration with several First Nations communities in Alberta, representing separate treaty areas across the province (continuous expansion of the RADAR model to additional First Nations communities is ongoing). We estimate that approximately 1000 people with type-2 diabetes currently reside in the pilot communities. All communities involved are several hours of travel from a major urban center, where the majority of diabetes specialist care services are located. Some communities have local family physician clinics, located just off reserve that also provide care for patients with diabetes; other communities have visiting family physicians on one or more days a week; while other communities have no local physician services, although services are available in neighboring rural communities. As a result, local, on-reserve, healthcare workers are the primary service providers delivering diabetes care and general health services for these populations. Prior to implementing RADAR, all communities were familiar with the CARE platform for the management of patient care within their respective communities.

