### Power and sample size

In prior studies, about 40% of diabetes patients will have at least a 10% improvement in A1c, BP, and cholesterol over time when studied under ‘usual care’[32]. To detect at least an additional 10% improvement in the proportion of patients achieving our primary endpoint under the RADAR model (i.e., move the population from 40% achieving endpoint to at least 50% achieving endpoint), at an alpha =0.05, an ICC of 0.01, we require 1153 total patients to detect a clinically important difference with 80% power. Assuming a 10% loss to follow-up, we require approximately 1250 total patients among our communities.

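### The stated 80% power is not supported by the plan's own figures: about 1250 patients are required, about 1000 are estimated in the pilot communities, and 1153 matches a parallel-arm formula rather than the stepped wedge

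*Protocol article*

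**What the plan says.** All places are in the protocol article.

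- *Power and sample size*: the effect is to "move the population from 40% achieving endpoint to at least 50% achieving endpoint". The requirement reads "at an alpha =0.05, an ICC of 0.01, we require 1153 total patients to detect a clinically important difference with 80% power". The next sentence inflates it: "Assuming a 10% loss to follow-up, we require approximately 1250 total patients among our communities". The section gives no cluster size, number of communities, number of steps, sidedness or formula.
- *Setting*: "RADAR involves collaboration with several First Nations communities in Alberta", and "We estimate that approximately 1000 people with type-2 diabetes currently reside in the pilot communities". The same paragraph says that expansion to more communities is continuing, without a number.
- *Eligibility and recruitment*: patients count in the evaluation only if they are 18 or older, had care at the facility in the last 1-2 years, consented verbally and were identified before the baseline phase ended.
- *Baseline 'control' phase* and *Intervention phase*: each community has a 6-month baseline and at least one year of intervention, ending on December 31, 2020 for all. Patients newly found during baseline are included.
- *Implementation and evaluation*: the design is a modified stepped wedge in which each community is its own control.
- *Data analysis*: the primary analysis includes enrolled patients with baseline data and carries the baseline value forward where follow-up is missing.

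**The concern.** Three figures that should fit together do not. The required number exceeds the only estimate of available patients. The allowance for loss does not return the number it is meant to protect. The uninflated total looks like the answer for a parallel-arm cluster trial, which this is not.

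The 80% figure is the article's only statement of precision. If it belongs to a trial of a different size and design, readers cannot tell how much a null result would mean. The Discussion also relies on the control periods to attribute improvement to RADAR, so the stated power will be read as describing that comparison.

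**Working it through.** **Inputs from the documents.** Proportions 0.40 and 0.50; alpha 0.05; power 80%; ICC 0.01; 1153 before loss; 10% loss; approximately 1250 after loss; about 1000 residents in the pilot communities.

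**Assumed, because not stated.** Two-sided test; patients per community m.

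**1. Reproducing 1153.** Pooled two-proportion formula, with p̄ = 0.45:

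n per arm = [1.96·√(2·0.45·0.55) + 0.842·√(0.40·0.60 + 0.50·0.50)]² / 0.10² = 387.3

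Two arms need about 774 (776 if each arm is rounded up). The parallel-cluster design effect is 1 + (m − 1)·ICC. With m = 50 it is 1 + 49·0.01 = 1.49, and 774 × 1.49 = 1153.3. At m = 50, 1153 patients means 1153/50, or about 23 communities.

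This choice is not unique. Any m from 46 to 54 comes within 3%. So do a continuity-corrected test with m about 42, a one-sided test with m about 90, 90% power with m about 12, and a paired before-after calculation with zero within-patient correlation and m = 200 (1166).

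**2. Trying the stated design.** The Woertman stepped-wedge design effect, with k steps, t measurements per step, b baseline measurements and n patients per community, is

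[1 + ρ(ktn + bn − 1)] / [1 + ρ(½ktn + bn − 1)] × 3(1 − ρ) / [2t(k − 1/k)].

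It was applied to 776 with ρ = 0.01, k = 2 to 10, t and b each 1 or 2, and n = 3 to 300. No setting came within 3% of 1153, whether patients or observations were counted. With t = b = 1 and 3 to 8 steps, one cohort measured in every period needs about 190 to 650 patients; total observations are about 1670 to 2590.

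**3. Loss.** 1153/0.9 = 1281.1, so 1282. In reverse, 1250 × 0.9 = 1125, which is 28 below 1153. The figure 1250 covers a loss of 1 − 1153/1250 = 7.8%.

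**4. Availability.** 1250 − 1000 = 250, a 20% gap. 1153 − 1000 = 153. Both gaps are before the eligibility and baseline-data limits.

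**5. Size on the apparent parallel formula** (design effect 1.49, illustration only):

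| Patients | Power for 40% vs 50% |
|---|---|
| 1153 | 80% |
| 1125 (1250 less 10%) | 79% |
| 1000 | 74% |
| 900 (1000 less 10%) | 70% |

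With 900 patients, 80% power is reached only for a difference of 11.3 points.

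**6. Size under a stepped wedge.** Hussey-Hughes power with 1000 patients in 4 to 10 communities (assumed counts) is 48-58% if each patient is counted once, and at least 98% if each is measured in every period. The power section does not say which applies.

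**The case against.** **The 1000 covers the pilot communities only.** Expansion is continuing, the 1250 is required across all the project's communities, and patients found during baseline add to the count. This stands: a reader might infer that the trial will fall short of its target, and the documents do not establish that. But the expansion has no number and is not tied to the sample size. It is also limited in time, since a 6-month baseline plus one year must fit before December 31, 2020, so a community would have to start by about mid-2019.

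**The parallel-arm powers do not apply to this design.** This also stands. A reader might infer from 74% or 70% that the trial is underpowered. The stepped-wedge range in step 6 lies on both sides of 80%, so neither a shortfall in power nor the stated 80% is shown.

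**Cluster size and formula may be in the full protocol.** That is fair, and their absence from an article is not the point here. A reader might infer that 1153 can only mean 50 patients per community, or that there should be 23 communities; step 1 shows that other choices reach it. Powers for communities of 100 or 150 would rest on an assumed community count and are not relied on.

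**The loss error is trivial.** Largely so: 1250 is approximate and within 2.5% of 1282, at a cost of about one power point. It is also argued that lost patients stay in the analysis through the carried-forward baseline. That keeps the denominator but can dilute the effect. If the 10% lost are assumed to show no treatment effect, the 10-point difference becomes 9, and all 1250 retained give about 75% on the parallel formula.

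**Conclusion.** The concern holds in this form: the stated sample size and 80% power do not follow from the article's own figures. The requirement of about 1250 is 250 above the only patient estimate given, with no stated reconciliation. The allowance for 10% loss should give 1282, which is a small error. The figure of 1153 fits a two-arm parallel cluster formula with a design effect near 1.49, and no stepped-wedge setting tried reproduced it.

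The sizes of 74% and 70% rest on three assumptions: a two-sided test, the design effect of 1.49, and enrolment limited to the pilot estimate (less 10% for the 70%). They show the scale of the inconsistency and are not estimates of this trial's power, which may be below or well above 80%.

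**What to change.** 1. If 1153 is kept, replace 1250 with 1282.
2. State how the required number relates to the roughly 1000 pilot patients: how many patients further communities are expected to add, and how many of all these will meet the eligibility and baseline-data conditions.
3. Restate power, or the detectable difference, for the patients and communities that can complete the 6-month baseline and at least one year of intervention by December 31, 2020. Compute it for the stepped-wedge cohort actually analysed, with the actual number of communities and steps, the period correlation and the within-patient correlation.
4. Name the formula and cluster size behind the final figure.

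The cost is a recalculation and some wording. No extra patients are needed. The stated power may become less favourable, unless the stepped-wedge calculation recovers it.

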### Data analysis

For quantitative data, all relative changes will be analyzed using the last known recorded value from the CARE platform from baseline to the end of the intervention phase. We will employ an intention-to-treat analysis, whereby all patients who are enrolled and have baseline data will be included in our primary analysis. The primary endpoint (i.e., 10% improvement in any of A1c, BP, cholesterol values from baseline or those maintaining values within 10% of baseline if at any or all three targets at baseline) will be evaluated using a conventional intention to treat analysis with logistic regression. However, if the observed intracluster correlation coefficient (ICC) is non-ignorable, we will use generalized estimating equations (GEE) that accounts for the clustered and hierarchical nature of our data [24]. Several a-priori subgroup analyses are planned for the primary endpoint. First, we will restrict analyses to patients not at target for any of the 3 primary outcome measures. Second, we will restrict analyses to those patients who were at target for each primary outcome measure (A1c, BP, cholesterol) to fully examine persistence at target over time. Additional subgroups of interest include analyses stratified by sex, and analyses stratified by age (<65 vs > =65 years). Secondary endpoints include: the proportion of clinical measures completed in accordance with guidelines (e.g., A1c, BP, cholesterol, foot and eye examination, receipt of vaccinations, smoking cessation counseling); the number of patients registered in CARE; and the proportion of patients linked to a health services provider.

We anticipate not having complete quantitative data on all endpoints of interest, given the real-world implementation of the project. Several approaches will be used for missing clinical data. First, in alignment with the intention-to-treat approach, we will use the baseline observation carried forward technique for our primary outcome. The stability of the results will be additionally evaluated using the multiple imputation method as a sensitivity analysis.

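### The sample size allows for 10% loss as if lost patients leave the analysis, but the primary missing-data rule keeps them in at baseline, so the 80% power claim needs restating

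*Protocol article*

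**What the plan says.** The Power and sample size section plans to "move the population from 40% achieving endpoint to at least 50% achieving endpoint", "at an alpha =0.05, an ICC of 0.01", and concludes that "we require 1153 total patients to detect a clinically important difference with 80% power". It then adds the loss allowance: "Assuming a 10% loss to follow-up, we require approximately 1250 total patients among our communities."

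The Data analysis section fixes the analysis set and the missing-data rule. On the set, "all patients who are enrolled and have baseline data will be included in our primary analysis". On missing values, "we will use the baseline observation carried forward technique for our primary outcome", with multiple imputation as a sensitivity analysis. The same section takes the last recorded value in the registry up to the end of the intervention phase. Baseline is therefore carried forward only where no later value exists.

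The Outcomes section counts a patient already at target as a success if that patient stays within 10% of baseline.

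**The concern.** Enlarging a sample for loss makes sense when lost patients contribute nothing to the analysis and the remaining patients still show the planned effect. Here a patient with no later value stays in the denominator with zero change. By the endpoint definition, that patient fails if off target at baseline and succeeds if at target, whatever RADAR did. The analysed number does not fall, but the expected difference does.

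At stake is how a null result would be read. If the 80% is taken at face value, a non-significant finding looks better powered than it was under the trial's own primary rule.

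**Working it through.** **Inputs from the Power and sample size section:** 40% v 50%, alpha 0.05 (taken as two-sided; not stated), power 80%, ICC 0.01 (cluster size not stated), N = 1153, 10% loss, N = about 1250.

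**Step 1: reproduce 1153.** The pooled two-proportion formula is

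n = [1.96·√(2p̄(1−p̄)) + 0.842·√(p1(1−p1) + p2(1−p2))]² / (p2−p1)²

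With 0.40, 0.50 and p̄ = 0.45 it gives 387.3 per condition, or 774.7 in total. Then 1153 / 774.7 = 1.488, which at ICC 0.01 corresponds to 1 + 0.488/0.01, or about 50 patients per cluster. So 1153 is consistent with the stated inputs, but the design effect is backed out of it and not independently confirmed.

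**Step 2: the loss step as the plan appears to intend it.** 1153/0.9 = 1281 and 1153 × 1.1 = 1268; 1250 is within 3% of both. If lost patients left the analysis, 1250 × 0.9 = 1125 would remain. At 40% v 50% and design effect 1.488, that gives 79.0% power, close to the stated 80%.

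**Step 3: the loss step under baseline carried forward.** Let d be the share of patients with no later value and q the share of those who are at target. The documents do not give q, so it is varied over its whole range. The analysed rates are

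p1 = 0.40(1−d) + dq and p2 = 0.50(1−d) + dq, so the difference is 0.10(1−d).

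All 1250 patients are analysed, giving 1250 / (2 × 1.488) = 419.9 effective patients per condition.

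| q | Power, d = 10% (difference 9 points) | Power, d = 5% (difference 9.5 points) |
|---|---|---|
| 0 | 75.8% | 79.6% |
| 0.3 | 75.0% | 79.3% |
| 0.5 | 74.6% | 79.1% |
| 0.7 | 74.4% | 79.0% |
| 1 | 74.2% | 78.8% |

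The d = 5% column is the case where half of the lost 10% have no later value and the other half contribute a last known value that reflects the full effect.

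**Step 4: variants.** With d = 10%, holding the number of clusters fixed, so that the design effect grows with N, gives 73.2-74.7%. A continuity-corrected calculation gives 74.3-75.8%. If 40% and 50% already count patients without follow-up, nothing is diluted further and 1250 gives 83.1%.

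**The case against.** The strongest objection is that a flat figure of 75% claims too much. Four parts of it carry weight.

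- **Last known value.** The analysis uses the last recorded value, and the intervention phase lasts at least a year, so some lost patients will have an interim measurement and will not be fixed at baseline. This stands. The 74-76% is the unfavourable end of a range, and with half of the lost patients measured later the shortfall from 80% is about one point or less.
- **What 40% and 50% refer to.** The text speaks of moving the population, which could mean everyone analysed. The source of the 40% cannot be checked here. The loss allowance points to rates in followed patients, since it would otherwise be unnecessary, but it does not settle the matter.
- **Equal dilution.** Each community is its own control, so loss may fall mainly in the intervention phase. With loss there only and d = 10%, the calculation at 1250 gives 31% at q = 0, 75% at q = 0.4, 83% at q = 0.5 and 94% at q = 0.7. The size, and even the direction, then depends on an unstated share. This stands as a stated assumption.
- **Design effect.** The 1.49 is derived, not quoted. It is, however, fitted to the plan's own 1153 at 80% power.

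None of this reconciles the two sections. Either lost patients are excluded, which the analysis rule does not do, or they are kept at baseline, which the loss allowance does not reflect.

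A reader might also infer a larger shortfall from the Setting section, which says that "approximately 1000 people with type-2 diabetes currently reside in the pilot communities". That does not follow. The figure refers to pilot communities, and the same section says that expansion to further communities is under way. Recruitment is a separate question.

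**Conclusion.** The mismatch is real: the loss allowance and the primary missing-data rule assume different analyses. Power at 1250 under the plan's own rule is about 74-76% if all of the lost 10% have no later value, and about 79-80% if half of them have none. The matching figure with lost patients removed is 79.0%, so the cost of the mismatch is at most about 4 to 5 points.

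These figures rest on three assumptions: 40% and 50% are rates in followed patients, both conditions are diluted equally, and the design effect implied by 1153 applies. A reader might conclude that the trial simply has 75% power. The documents do not support that as a single figure, because they give neither the share of lost patients with a later value nor the basis of the 40%. The point is worth correcting but moderate: it concerns the stated power, not the validity of the primary analysis.

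**What to change.** In the Power and sample size section:

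1. Compute the power at 1250 under the baseline-carried-forward rule. Report it as a range of roughly 74-80%, naming the share of lost patients assumed to have no later value, the equal dilution of both conditions, and the design effect or cluster size used.
2. State whether 40% and 50% already count patients without follow-up. If they do, remove the loss inflation and report about 83% at 1250.

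The cost is a recalculation and a few sentences, and the stated power may read slightly less favourably. The enrolment target and the choice of primary missing-data method can stay as they are.

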## Discussion

It is well known that diabetes care is suboptimal in First Nations populations [4–6]. Our own research [20, 32], coupled with other large-scale research projects across the country, has clearly demonstrated the need for improved care in this high-risk population [5, 6]. We will evaluate the effectiveness of RADAR in improving the quality of care for First Nations people with type-2 diabetes living on reserve. The aim of RADAR is to improve processes of care, and ultimately clinical outcomes in patients, and to build local capacity and expertise in the management of diabetes. The current Canadian Diabetes Association Clinical Practice Guidelines strongly advocate for multidisciplinary teams to improve outcomes in people with diabetes [8], yet these multidisciplinary teams are often lacking in First Nations communities [5]. We believe RADAR, including the CARE platform and CC model, can facilitate a culturally relevant community-based multidisciplinary team approach to diabetes care.

There are several strengths related to our implementation and evaluation of RADAR. First, the RADAR model is well positioned to succeed in the communities based on prior work by our team. OKAKI Health Intelligence Inc. has been successfully working in First Nations communities in the province for over 7 years. This partnership reinforces that RADAR is community-specific, culturally relevant and promotes its sustainability. Moreover, the communities have already adopted the CARE platform for other aspects of patient care (e.g., home care). Therefore, the extension of the CARE platform to chronic disease management is highly feasible.

Second, our use of the RE-AIM framework will provide insight into the broader impact of RADAR beyond clinical effectiveness and identify both facilitators and barriers to implementing RADAR within each community. These results will help inform scale and spread of RADAR to other suitable communities and populations.

Third, we will employ a valid stepped wedge study design. Often quality-improvement projects show benefit when evaluated, but are conducted without a robust comparison group, making assessment of the true absolute improvements in care difficult to decipher. By including control periods over time, we will be able to elucidate any improvements directly attributed to the RADAR model.

Regardless, there are design features of RADAR that warrant further discussion. First, we have used process (i.e., intermediate or surrogate) outcomes as measures of quality, rather than harder clinical endpoints (e.g. diabetic complications like amputation, heart attack or stroke). We chose these process endpoints, as we do not expect to observe changes in hard clinical outcomes over the short timeline of this project. Nevertheless, reductions in these outcomes (e.g. A1c, BP, cholesterol, etc.) are well established in many large scale RCTs as conferring substantial benefits on either macro- or microvascular outcomes and are recommended in the Canadian Diabetes Association Clinical Practice Guidelines [8, 32]. Moreover, our objective is to determine if RADAR can influence these clinical measures, not reaffirm if these changes are important on hard clinical endpoints. If the intervention improves these outcomes, hard clinical endpoints would be expected to also change (e.g. heart attacks and stroke) over time.

Second, our economic models cannot be fully populated by our results. This is true of most models and we will need to make assumptions based on literature and expert opinion. However, our proposed economic approach is peer-reviewed and published and we have used it in previous analogous analyses [21, 22]. We will also undertake many sensitivity analyses to demonstrate the results are robust and valid.

Last, we have designed a pragmatic and feasible controlled project rather than a randomized controlled efficacy trial. Our project is a community-based intervention aimed at the local healthcare workers as opposed to patients *per se*. Individual patients could not be randomized to care with and without RADAR because of the threat of “contamination” (i.e., patients within a community health facility would likely be exposed to some aspects of the intervention regardless of study arm). Similarly, randomization could not occur at the level of the local healthcare workers for similar reasons (e.g., increased knowledge on the appropriate care of patients with diabetes would be expected to diffuse throughout the entire care team in a health facility). Moreover, acceptance of a community to a traditional randomized control trial would be expected to be low, as few communities would be accepting of being the control community for extended durations. The stepped wedge design will be morally and politically more acceptable to the communities, and because of logistical, practical, and financial constraints, it can be better implemented in stages. Furthermore, the proposed design incorporates a number of methods other than random allocation to protect internal validity (e.g., controlled before after with sequential roll-out to reduce time-related biases), and the design is considered valid and included in the Cochrane EPOC Systematic Reviews. The results from our project may have greater applicability than the results of a randomized trial in a highly selected and potentially biased sample.

